## Abstract

**Background:**

Alcohol use is a major public health challenge in France, where at the age of 17 half the young people report an episode of severe alcohol intoxication in the month preceding the survey. Numerous prevention programmes have a general objective, but in adolescence individual vulnerabilities towards addictions differ significantly with personality traits. Prevention targeting personality traits enables work on risk factors for addictive behaviours, and has shown genuine efficacy.

Among existing programmes, PREVENTURE has shown an effect on the reduction in alcohol consumption by targeting four personality traits: impulsivity, sensation-seeking, negative thoughts and anxiety. This programme has been tested on samples recruited in adolescent populations in school environments, identifying adolescents at risk, but it has not been tested on a more targeted recruitment of adolescents seen in consultation.

**Methods:**

The main hypothesis of this study is that the targeted prevention programme PREVENTURE will have an impact on the prevalence of binge-drinking episodes. The secondary hypotheses explore other factors such as associated substance use, anxiety and depression, as well as the acceptability of the programme. This article presents the study protocol of “PREVADO” study.

We intend to assess the impact of the targeted intervention programme PREVENTURE on the prevalence of binge-drinking episodes among adolescents aged 14 to 17 years consulting in one of the participating centres or referred by a school doctor. The study will be prospective, randomised, controlled and open-label, and will comprise an intervention group and a control group.

The adolescents will then be followed and assessed 1, 3, 6 and 12 months after the intervention.

The study needs to include 700 subjects in order to reach 340 adolescents randomised, 170 in each group. It will concern 33 centres.

**Discussion:**

This project could favour the targeting of addictive behaviours among vulnerable adolescents, and its application on a larger scale could be envisaged.

**Trial registration:**

The Trial registration number is NCT04599270, and it was registered on the ClinicalTrials.gov public website.

## Background

Alcohol use is considered as a leading risk factor in the global burden of disease and causes substantial damage to health [1–3]. Four per cent of the global burden of disease is attributable to alcohol [4]. Excessive alcohol consumption results in 3.3 million deaths each year, 5.9% of all deaths around the world [5]. Alcohol consumption tends to emerge during adolescence, and is especially risky for adolescents given its impact on the developing brain [1]. Moreover, from the very first episodes of alcohol consumption, intensive binge drinking can cause severe damage in the short and medium to long term [2, 3], such as alcohol-induced coma, involvement in interpersonal violence as a victim and/or as a perpetrator, non-consensual sexual acts, road accidents, etc. [4, 5]. Evidence suggests that an early onset of alcohol use increases the risk of alcohol use disorders in later life and comorbid mental health problems [6].

In Europe, in 2019, 79% of students reported having consumed alcohol at least once during their lifetime and 13% of the students in the ESPAD study reported having been intoxicated in the last 30 days prior to survey [7]. In France more particularly, nearly 80% of those aged 14 had already experimented alcohol in their lifetime [8], and half of the adolescents aged 17 reported a binge drinking episode in the last month (over 5 standard drinks on the same occasion) [9].

Social and cultural factors influence consumption and lead to a social valuation of alcohol consumption and binge drinking [9, 10]. There are also individual vulnerability factors, particularly marked in adolescence in the transition from experimentation to regular use or even alcohol use disorders (AUD) [11]. Despite the extent of the damage, there is currently little reliable data on efficacious primary prevention strategies for dealing with addictive behaviour [12]. Many prevention programmes target age groups in schools, to delay or reduce the use of psychoactive substances or the harm associated with their use. However a meta-analysis on the impact of school-based prevention programmes concluded that most interventions were associated with little or no impact in terms of reducing substance misuse among adolescents [13].

During adolescence, individual vulnerability with regard to the risk of addictive disorders differs significantly according to personality traits [14]. Targeted prevention on the basis of personality entails work on the risk factors of addictive behaviour (tobacco, alcohol, cannabis, etc.) and has proved to be highly efficacious in terms of reducing consumption, damage and alcohol acceptability among adolescents [15].

Among existing programmes, the *Preventure* program has been evaluated in 5 trials with high-risk adolescents identified in school settings accross different countries (Canada, Europe, Australia) [10–14]. *Preventure* is a preventative program that utilizes Cognitive behavioural therapy (CBT) techniques and motivational interviewing (MI) strategies. This program is selectively administered in schools to adolescents identified as at risk for addictive disorders by targeting four personality risk factors: negative thinking, anxiety sensitivity, impulsivity and sensation-seeking [15]. Preventure was originally designed to target substance use prevention and findings across the literature have demonstrated clear and robust effects on the reduction of alcohol consumption [8, 16–19]. This programme has been studied in different adolescent samples recruited from the community (i.e., schools), identifying at-risk adolescents.

Nevertheless, *Preventure* has never been tested among adolescents who are neither seeking treatment nor have been identified as at risk by school nurses or medical doctors. A recent review highlighted the need to make this program more accessible by targeting adolescents pre-identified as vulnerable and by studying the impact of the programme on such populations [15]. This strategy could enable adolescents who have left school and adolescents with higher vulnerabilities to have access to the program.

The current randomized controlled trial was designed to evaluate the impact of the *Preventure* program on adolescents (i.e., age between 14 and 17), in comparison to usual follow-up care for adolescents (i.e., identified in primary care, or in adolescent care or through school nurses or doctors).

The main hypotheses of this study are that 1. the *Preventure* program will potentially have an impact on 1/ the prevalence of binge drinking episodes 2/ the number of days of alcohol consumption, 3/ associated substance uses: tobacco/ cannabis, 4/ anxiety and depression, 5/ alcohol-related harm, and 6/ quality of life. Moreover, it is also hypothesized that the Preventure program will be considered as an acceptable intervention among French adolescents.

This project could promote the targeted prevention of addictive behaviours among vulnerable adolescents. Thus, the use of the Preventure program could be considered on a larger scale and developed in primary care and schools or adolescent care facilities in France.

This article presents the study protocol; it follows the Standard Protocol items: recommendations of the 2013 Interventional Trial (SPIRIT) guidelines [16].

## Methods/design

### Aim of the study

The main objective of the current study is to evaluate the impact of the *Preventure* program on the prevalence of binge-drinking episodes (i.e, defined as more than 5 standard units of alcohol on a single occasion) among adolescents aged between 14 to 17 and at risk of developing problematic alcohol use, in comparison with usual follow-up care. The secondary objectives are to assess the impact at different times of follow up (3, 6 and 12 months) on 1/ the number of days with alcohol consumption 2/ associated substance uses: tobacco/cannabis, 3/ anxiety and depression, 4/ alcohol-related harm, 5/ quality of life at each stage, 6/ the acceptability of the intervention among French adolescents.

### Study setting

This study will take place in the western region of France, in primary care settings, in specialized adolescent care settings and in schools (school nurses and doctors). Information and poster campaigns will be disseminated within the networks, to the schools concerned and to the general public. This dissemination will enable the public concerned to be broadly informed.

### Participants and materials

All adolescents aged 14 to 17 years seeking treatment, for any reason, in the networks involved or identified by the school medical staff and meeting the inclusion criteria will be offered the opportunity to participate in the study.

### Inclusion criteria

Adolescents aged 14 to 17 years, seeking treatment in one of the participating centres in primary care, or adolescent care facilities (general or addictive disorder consultations for adolescents) or identified by a school doctor or nurse, who have already experienced alcohol (at least 1 standard unit of alcohol lifetime), will be included in the study, after written and informed consent from the parents and the adolescents. They are required to have Internet access, access to a smartphone, tablet or computer.

### Non-inclusion criteria

The non-inclusion criteria will be the following: adolescents expressing refusal to participate in the study, or presenting moderate-to-severe substance use disorders (other than tobacco) or current non-stabilized psychiatric disorders, or current treatment for severe substance use disorders and/or severe psychiatric disorders (psychotic disorders, autistic disorders), or inadequate understanding of the French language. A lack of internet access, access to a smartphone, tablet or computer will also be a non-inclusion criterion.

### Exclusion criteria

Adolescents who are not at risk of developing problematic substance use according to the negative thinking, sensitivity to anxiety, impulsivity and sensation-seeking dimensions of the SURPS (Substance Use Risk Profile Scale) will be excluded from the study (cut-offs: ≥14, ≥17, ≥15, ≥13 respectively) [8].

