### Consent

The investigator will provide complete verbal and written information to the patient and parents, checking the inclusion and non-inclusion criteria. Once eligible adolescents and their parents who have given their verbal consent, they will be referred to the study psychologist who will obtain the written consent of the parents and the adolescent. Subjects will be able to withdraw their consent and request to be removed from the study at any time for any reason. The investigator may temporarily or permanently discontinue a subject’s participation in the study for any reason that would be in the best interests of the subject, particularly in the case of serious adverse events. If a subject is lost to follow-up, the investigator will make every effort to re-establish contact with the person. In the case of a withdrawal of consent, the data collected will not be used in accordance with the patient’s wishes.

During their participation, patients will not be able to participate in research on addictive behaviours, and there are no restrictions on treatment.

An assessment of personality characteristics that represent a risk for the development of problematic substance use using the SURPS questionnaire will be carried out. Only adolescents with risk-related personality traits, according to at least one of the dimensions: negative thinking, sensitivity to anxiety, impulsivity and sensation-seeking on the SURPS, will be randomized. The others will be excluded from the randomized trial. Adolescents excluded prior to randomization will have a meeting with a psychologist to discuss the risks associated with addictive disorders and they will be given information about risk prevention.

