### Randomisation

Adolescents will be randomised [1], and the randomisation will be stratified according to the predominant type of risk-prone personality trait (4 types) presented by the adolescents and according to recruitment conditions (school care vs. primary or specialised adolescent care). The control group will receive the usual routine follow-up (individual consultations in primary care / or in adolescent care facilities/ adolescent addictive disorder consultations) and assessments.; The intervention group will receive the usual follow-up, assessments plus the Preventure program tailored to one personality type among the 4 risk-related personality traits.

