### SURPS: substance use risk profile scale

The Substance Use Risk Profile Scale (SURPS) is a screening instrument for personality traits identified as related to the risk of developing of addictive disorders. The SURPS consists of 23 items assessing four dimensions: Impulsivity, sensation-seeking, negative thinking and anxiety. The SURPS was created by Woicik et al. [17] and includes 23 items, to which young people are asked to respond using a 4-point Likert scale, ranging from strongly agree to strongly disagree: negative thinking (7 items), sensitivity to anxiety (5 items), impulsivity (5 items) and sensation-seeking (6 items).

The four different personality dimensions measured are associated with a high risk of developing addictive disorders. It was validated in French on a population of students from Quebec. The psychometric properties of the French version were satisfactory and comparable to previous studies and to the original version. The thresholds defined as risk-related were calculated according to means and standard deviations, and for the French version are: Negative thoughts = 15; Anxiety = 13; Impulsivity = 14; Sensation seeking = 17 [8].

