### Sample size

On the basis of the results observed in the publication by Lammers et al. [13], 50% of adolescents who have had at least one binge-drinking episode in the last month are expected in the control arm while 35% are expected in the intervention group. With an alpha risk of 0.05 and a potency of 80%, the sample size should be 170 patients/group, or 340 patients in all. As the expected proportion of “at-risk” subjects (who will be randomised) is of the order of 1 in 2 among the adolescents included, an initial number of 700 adolescents is planned to be included (including a proportion of subjects not evaluated for the main criterion).

Thirty-three centres will be included, distributed across 8 hospital structures and the general medicine network, corresponding to less than one patient/month per investigator.

The duration of the inclusion period will be 36 months, the duration of participation for each patient will be 15 months, and the total duration of the study will be 51 months.

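### The SURPS cut-offs that decide who is randomised are stated in two incompatible trait-by-trait pairings

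*Protocol article*

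**What the plan says.** The Exclusion criteria section removes adolescents who are not at risk "according to the negative thinking, sensitivity to anxiety, impulsivity and sensation-seeking dimensions of the SURPS". It then says that they "will be excluded from the study (cut-offs: ≥14, ≥17, ≥15, ≥13 respectively". The closing word fixes the pairing: negative thinking ≥14, anxiety ≥17, impulsivity ≥15, sensation-seeking ≥13.

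The section on the Substance Use Risk Profile Scale gives the French risk thresholds as "Negative thoughts = 15; Anxiety = 13; Impulsivity = 14; Sensation seeking = 17 [8". Both places cite the same reference.

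The Consent section makes these thresholds the condition for randomisation: "Only adolescents with risk-related personality traits, according to at least one of the dimensions" are randomised, and the others leave the trial. The Randomisation section then has allocation "stratified according to the predominant type of risk-prone personality trait (4 types". The Sample size section expects about one in two included adolescents to be at risk, and from that plans 700 inclusions for 340 randomised.

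**The concern.** Both lists are complete and each ties every number to a trait, so this is neither a broken table nor a detail left to a fuller document. The rule is stated twice, and the two statements cannot both be followed.

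The rule decides who is randomised. Staff working from one section would admit adolescents whom staff working from the other would turn away, and the reverse. The population to which the result applies would then depend on which section was used, and so would the number of inclusions needed to reach 340 randomised. Readers of the eventual report could not tell from this article which adolescents the trial was meant to study.

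**Working it through.** **1. The two lists side by side.** I read both as *at or above*; the SURPS section writes only an equals sign.

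| Trait | Exclusion criteria | SURPS section | Difference |
|---|---|---|---|
| Negative thinking | 14 | 15 | −1 |
| Anxiety | 17 | 13 | +4 |
| Impulsivity | 15 | 14 | +1 |
| Sensation-seeking | 13 | 17 | −4 |

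All four disagree. If the SURPS figures meant *strictly above*, impulsivity would agree (15 and 15) and the other three would still conflict.

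**2. Where the mismatch probably comes from.** Both lists use the same four numbers: 13, 14, 15, 17. Of the 4! = 24 possible trait orders, exactly one makes 14, 17, 15, 13 match the SURPS section: impulsivity, sensation-seeking, negative thinking, anxiety. The SURPS section opens in that order, "assessing four dimensions: Impulsivity, sensation-seeking, negative thinking and anxiety", and the Abstract uses it too. Numbers kept in one order beside traits listed in another would produce exactly this result.

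**3. Plausibility against the scale ranges.** The item counts are "negative thinking (7 items), sensitivity to anxiety (5 items), impulsivity (5 items) and sensation-seeking (6 items" on a 4-point scale. Assuming items are coded 1 to 4, the ranges are 7–28, 5–20, 5–20 and 6–24. The relative position of a cut-off is (cut-off − minimum) / (maximum − minimum):

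- Negative thinking: 7/21 = 0.33 (Exclusion criteria), 8/21 = 0.38 (SURPS section)
- Anxiety: 12/15 = 0.80, 8/15 = 0.53
- Impulsivity: 10/15 = 0.67, 9/15 = 0.60
- Sensation-seeking: 7/18 = 0.39, 11/18 = 0.61

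As written, the exclusion criterion puts anxiety near the top of its range and sensation-seeking below its midpoint of 15. The SURPS section is more even (0.38 to 0.61). This is supporting evidence, not proof.

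**4. Who is affected.**

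- Randomised under Exclusion criteria, excluded under the SURPS section: the only raised score is sensation-seeking 13–16 or negative thinking 14.
- Excluded under Exclusion criteria, randomised under the SURPS section: the only raised score is anxiety 13–16 or impulsivity 14.

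**5. The plan's own sample size.** The Sample size section says 50% "are expected in the control arm while 35% are expected in the intervention group". With two-sided alpha 0.05 (sidedness is not stated), 80% power and no continuity correction:

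n = [1.96·√(2·0.425·0.575) + 0.8416·√(0.50·0.50 + 0.35·0.65)]² / 0.15² = (1.370 + 0.582)² / 0.0225 ≈ 169.3, rounded up to 170.

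The stated 170 is reproduced (power at 170 is 0.802). No SURPS quantity enters, so it does not change. The at-risk share, 340/700 = 48.6%, does depend on the cut-offs.

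**6. Illustrative size.** The article gives no score distributions. I assumed normal subscale scores, rounded, with all four means at the same relative position (30%, 40% or 50% of the range), SD 15% or 20% of the range, and inter-trait correlation 0 or 0.2. That makes twelve settings.

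- Share at risk on at least one trait: 63–99% under Exclusion criteria, 42–96% under the SURPS section. The exclusion list is looser in every setting, by 2 to 21 percentage points.
- Eligibility differs for 4.3% (3.5 + 0.8) to 28.7% (24.9 + 3.8) of those screened.
- With means at 30% of the range, the SURPS list gives 42–57%, close to the planned one in two. The exclusion list then gives 63–70%, and eligibility differs for 21–29%.

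**The case against.** The strongest reply is that this is a slip in a condensed article. Screening uses the SURPS questionnaire itself. If the form and the randomisation system carry the thresholds of the SURPS section, nobody was misclassified and only a printed line is wrong. That stands as a possibility, but the article does not show which list is in use.

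Four stronger readings are tempting, and the document does not support them.

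- *The trial is randomising the wrong adolescents.* This needs the SURPS section to be the intended list and the exclusion list to be the one applied. The first is likely from step 2 but cannot be proved without the cited source; the second is unknown.
- *The anxiety stratum would almost vanish.* If the SURPS thresholds sat one SD above the mean, with SDs of 2.5 to 4 and a half-point correction, the exclusion list would flag anxiety in only about 0.8–3% and sensation-seeking in about 55–79%. But strata and modules follow the predominant trait, and the article does not say that predominance is set by these cut-offs. An adolescent admitted on one trait could still be classed under another.
- *The exclusion list departs from validated thresholds.* The article says that the French version was validated and that the thresholds were calculated from means and standard deviations. It does not say that the thresholds themselves were validated.
- *A given percentage of those randomised would be ineligible.* Such figures move with the assumed distribution. Even the share flagged per trait under the SURPS section, with thresholds at mean plus one SD, is about 16% for plain normal scores and about 19–21% with a half-point correction.

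**Conclusion.** The concern holds as an internal inconsistency in an eligibility threshold. The two sections disagree on all four traits, by 1, 4, 1 and 4 points, and nothing else in the article resolves it. The exclusion criterion is probably the mis-paired one, but the document alone cannot settle that.

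The firm part is the set of discordant score bands in step 4; which group is misclassified depends on which list was intended and which was applied. How many adolescents fall in those bands is not known: 4% to 29% of those screened is an illustration resting on assumed distributions. The direction (exclusion list looser overall) held in every setting tried, but those settings place all four traits at the same relative position. The 170 per group is unaffected. The one-in-two planning share, and so the 700 inclusions, is affected. Because the text governs entry to randomisation and costs little to correct, it must be fixed.

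**What to change.** - Replace the two statements with one trait-by-trait list, each number beside its trait and each written as *at or above* or *strictly above*, checked against the cited source. The Exclusion criteria and SURPS sections should both refer to it.
- Confirm which list is printed on the screening form and programmed in the randomisation system, and whether it was the same at all centres throughout.
- State whether the predominant trait is derived from the cut-offs or from relative scores, so that any effect on strata and modules can be judged.
- If any participant was screened with the other list, re-score from the stored SURPS items, report how many randomised participants fall outside the reconciled rule, and add a sensitivity analysis of the main criterion in those eligible under it. Also report how many adolescents were excluded who would have qualified; re-scoring can count them but cannot restore them to the trial.
- Compare the observed at-risk share with the planned one in two, and revise the 700 if they differ.

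The cost is one corrected list and one system check. Re-scoring needs no new data collection provided the item responses were kept.
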